**7.2.7 Documenting and Reporting of Pregnancy**

Subjects will be counseled to inform the investigator of any pregnancy that occurs during study treatment and for 90 days after the last dose of study drug/s.

If a subject or the female partner of a male subject becomes pregnant while participating in the study, study treatment must be permanently discontinued immediately. The investigator must notify the Sponsor's Medical Monitor and ICON Pharmacovigilance within 1 business day of the sites' knowledge of the subject's (or partner's) pregnancy, by utilizing the Pregnancy Initial Report Form. If confirmed to be on active drug, the subject or partner will be followed until end of pregnancy and the infant will be followed for 1 year after the birth, provided informed consent is obtained. A separate informed consent form will be provided to explain these follow-up activities. Pregnancy itself does not constitute an adverse event.

**7.3 FOLLOW-UP OF ADVERSE EVENTS AND SERIOUS ADVERSE EVENTS**

Follow all AEs (serious and non-serious) until resolution or otherwise explained, the subject dies, the event stabilizes and is not expected to further resolve, or when alternative therapy is instituted, whichever occurs first. If alternative therapy is instituted, it should be documented. Alios BioPharma may request that the investigator perform or arrange for supplemental measurements or evaluations to further clarify the nature of the event.

**7.4 SPONSOR'S REVIEW OF ADVERSE EVENTS AND SERIOUS ADVERSE EVENTS**

Alios BioPharma will maintain an ongoing review of all AEs and SAEs. The PK/PD relationship between AL-335 and its metabolites and various safety parameters including ECG changes, vital signs, and relevant laboratory parameters will be evaluated.

**7.5 EMERGENCY UNBLINDING FOR PARTS 1 AND 2 (SAD AND FOOD EFFECT)**

Randomization codes will be given to the site pharmacist at the start of the study and maintained in a secure location. Treatment assignment will be made available to the PI in the event of a medical emergency or an adverse event that necessitates identification for

the welfare of a subject. Whenever possible, the PI will contact the Sponsor to discuss the need to break the blind prior to proceeding with unblinding. The PI will notify the sponsor as soon as is practical in the event of the study blind being broken and will document the reason.

## **7.6 EMERGENCY UNBLINDING FOR PART 3 (MAD)**

Randomization information will be made available to the pharmacist for the subjects enrolled at their site. The treatment assignments will be made available to the PI in the event of a medical emergency or an adverse event that necessitates identification for the welfare of a subject. Whenever possible, the PI will contact the Sponsor to discuss the need to break the blind prior to proceeding with unblinding. The PI will notify the sponsor as soon as is practical in the event of the study blind being broken and will document the reason.

## **8.0 STUDY VARIABLES AND MEASUREMENTS**

### **8.1 EFFICACY VARIABLES/MEASUREMENTS**

Serum HCV RNA will be measured in subjects with CHC infection. No efficacy variables will be evaluated in the healthy volunteer cohorts.

### **8.2 SAFETY VARIABLES/MEASUREMENTS**

Safety evaluation will include AEs and SAEs, vital signs, laboratory tests (including hematology and serum chemistries), ECG, physical examination, urinalysis, and pregnancy tests.

#### **8.2.1 Adverse Events**

Adverse events, including pretreatment events, will be recorded from the time of consent through 21 days after the last dose of study drug. All AEs/SAEs will be coded using the *Medical Dictionary for Regulatory Activities (MedDRA)*.

#### **8.2.2 Clinical Laboratory Measurements**

Clinical laboratory variables, including hematology, serum chemistries, urinalysis, and pregnancy testing, will be assessed at screening. Hematology, serum chemistries, and pregnancy testing will be evaluated periodically during the study as indicated in this protocol.

#### **8.2.3 Prior and Concomitant Medications**

Use of all medications and supportive therapy from within 21 days of the screening visit through study completion will be recorded. All concomitant medications will be mapped using the World Health Organization (WHO) Drug Dictionary.

### 8.3 PHARMACOKINETIC MEASUREMENTS

Predose and postdose plasma and urine samples will be collected from subjects in all dosing cohorts at specified times throughout the study for the determination of PK parameters for AL-335 and its metabolites (timepoints specified in Section 6.1, *Study Procedures, Schedule of Events*). Plasma and urine concentrations of study medication and metabolites will be assessed by a liquid chromatography tandem mass spectrometry method and used to calculate the values of PK parameters, including:

|                       |                                                                                                             |
|-----------------------|-------------------------------------------------------------------------------------------------------------|
| Ae                    | Total amount excreted in urine                                                                              |
| AUC 0-inf  | Area under plasma concentration-time curve from hour 0 to infinity                                          |
| AUC 0-last | Area under plasma concentration-time curve from hour 0 to last sample with measurable plasma concentrations |
| AUC 0-tau  | Area under plasma concentration-time curve over one dosing interval                                         |
| C last     | Last measurable plasma concentration                                                                        |
| C max      | Maximum observed concentration                                                                              |
| C min      | Minimum observed concentration (for repeated doses)                                                         |
| Cl R(0-t)  | Renal clearance over 0 to t time period                                                                     |
| CL                    | Systemic clearance                                                                                          |
| CL/F                  | The apparent oral clearance                                                                                 |
| λ z        | terminal elimination rate constant                                                                          |
| t 1/2      | Terminal elimination half-life                                                                              |
| t last     | Time to last measurable plasma concentration                                                                |
| t max      | Time of maximum concentration                                                                               |
| V d        | Volume of distribution                                                                                      |
| V z /F     | The apparent steady-state volume of distribution                                                            |

### 8.4 PHARMACODYNAMIC MEASUREMENTS

Blood samples for HCV viral load measurements will be collected for assessment in subjects with CHC as outlined in [Table 6.1-3](#).

### 8.5 VIRAL RESISTANCE

Blood samples will be collected from subjects with CHC to assess the potential emergence of viral resistance to AL-335.

## 9.0 STATISTICAL CONSIDERATIONS

### 9.1 GENERAL CONSIDERATIONS

Continuous data will be summarized by descriptive statistics, including number of subjects, mean, standard deviation, median, and range. Categorical data will be summarized by the number and percentage of subjects. Time-to-event endpoints will be estimated using the Kaplan-Meier method. All analyses will be presented by dose cohort and the combined study population.

Details will be provided in the statistical analysis plan (SAP). The Clinical Study Report (CSR)

may be written in two stages for this study; one for the SAD and Food Effect portions (Parts 1 and 2) and another for the MAD phase (Part 3).

## 9.2 STUDY ENDPOINTS

### 9.2.1 Primary Endpoint

Analysis of safety measures including but not limited to tabulation of treatment emergent adverse events, physical examination findings, vital signs, 12-lead ECGs, and clinical lab results (including chemistry, hematology, and urine).

This endpoint may be characterized by analyzing the number of participants with adverse events per type as a measure of safety and tolerability after increasing single oral doses in HV, as well as analyzing the number of participants with adverse events per type as a measure of safety and tolerability after 7 days of oral dosing in subjects with CHC infection.

### 9.2.2 Secondary Endpoints

PK parameters of AL-335, ALS-022399, ALS-022227 (and other metabolites if applicable) following single dose administration:  $C_{max}$ ,  $t_{max}$ ,  $t_{1/2}$ , CL/F and  $V_z/F$  (for AL-335 only),  $AUC_{0-inf}$  or  $AUC_{last}$

PK parameters of AL-335, ALS-022399, ALS-022227 (and other metabolites if applicable) following repeat dose administration:  $C_{max}$ ,  $t_{max}$ ,  $t_{1/2}$ ,  $AUC_{last}$  and  $AUC_{0-tau}$

PK parameters of AL-335, ALS-022399, ALS-022227 (and other metabolites if applicable) following single dose administration in tablet form as compared with suspension:  $C_{max}$ ,  $t_{max}$ ,  $t_{1/2}$ , CL/F and  $V_z/F$  (for AL-335 only),  $AUC_{0-inf}$  or  $AUC_{last}$

PK parameters of AL-335, ALS-022399, ALS-022227 (and other metabolites if applicable) after a single oral dose in HV in fasted conditions as compared with fed conditions

Concentration in urine and urinary excretion of AL-335, ALS-022399, ALS-022227 (and other metabolites if applicable) after a single oral dose in HV in fasted conditions

HCV RNA viral load change from baseline in subjects with CHC infection

Sequence analysis of the HCV NS5B region in subjects with CHC infection, as appropriate

## 9.3 DETERMINATION OF SAMPLE SIZE

No formal sample size calculations have been performed as this is an exploratory study. The number of subjects participating in each cohort is considered sufficient to achieve the objectives of the study. Approximately 40 (up to 64) healthy subjects, and 70 (up to 80) subjects with CHC infection will be evaluated in this study.

The number of subjects is considered sufficient to support PK and safety assessments, however as this is a small study no sample size calculation was performed. Three additional doses in the SAD and one additional in the MAD part of the study may be enrolled at the

discretion of the Sponsor and Principal Investigator (PI) based on the emerging PK profile and the presence of an acceptable safety profile.

## **10.0      RANDOMIZATION**

In Part 1, approximately 40 (up to 64) subjects will be assigned to up to 8 single-dose cohorts of 8 subjects each. For each dose cohort, 8 subjects will be randomized in a 3:1 ratio to receive AL-335 or placebo.

For Part 2, subjects in Cohort 3 from Part 1 will receive the same assignment for their second dose.

In Part 3, approximately 70 (up to 80) subjects with CHC infection will be enrolled. For each dose cohort, 10 subjects will be randomized in a 4:1 ratio to receive AL-335 or placebo.

Subjects will not be stratified by any baseline characteristics.

## **10.1      STUDY CONDUCT**

### **10.1.1      Subject Disposition**

An accounting of all subjects over the course of the study will be reported by dose cohort. Enrollment, study drug administration, subject completion, premature discontinuation, and major protocol violations will be tabulated and summarized by dose cohort.

### **10.1.2      Replacement of Subjects**

All 8 HV subjects and at least 8 of the 10 subjects with CHC infection must complete the dosing schedule for each cohort. A decision to replace subjects will be made by the Sponsor in consultation with the PI. Subjects withdrawn for safety reasons will not be replaced.

### **10.1.3      Procedures for Handling Missing, Unused, or Spurious Data**

Strategies for handling missing, unused, or spurious data will be specified in the SAP.

## **10.2      ANALYSIS DATA SETS**

The Full Analysis Set (FA) is defined as all enrolled subjects who have received at least one dose of study medication. Further analysis data sets will be defined for each part of the study in SAP.

## **10.3      DEMOGRAPHICS AND BASELINE CHARACTERISTICS**

Demographic data (age, sex, ethnicity, body weight) and baseline disease characteristics will be tabulated and summarized by dose cohort and presented in data listings.

## **10.4 SAFETY ANALYSIS**

### **10.4.1 Adverse Events**

The MedDRA medical dictionary will be used to map the AE/SAE verbatim terms to specific system organ classes (SOC) and preferred terms. Adverse events and SAEs will be summarized in summary tables and tabulated in by-subject listings by SOC and preferred term for each dosing cohort and by treatment assignment (AL-335 or placebo). Incidence rates will be presented.

### **10.4.2 Vital Signs, ECG, Physical Examination, and Laboratory Assessments**

Vital signs, including resting pulse, blood pressure, and body temperature, will be summarized and tabulated by dosing cohort and by treatment assignment (AL-335 or placebo). The proportion of subjects with abnormal findings based on physical examinations over time will be summarized by dosing cohort and by treatment assignment (AL-335 or placebo). Laboratory values will be graded and summarized based on CTCAE v3.0. Number and percentage of subjects with Grades 3 and 4 laboratory abnormalities will be tabulated by dosing cohort and by treatment assignment (AL-335 or placebo).

In the event a safety signal is detected, the PK/PD relationship between AL-335 and its metabolites and various safety parameters including ECG changes, vital signs, and relevant laboratory parameters will be evaluated.

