- Genotypes 4-6: a cohort of ten (10) treatment naïve subjects with genotypes 4-6 CHC infection will be enrolled (8 assigned to AL-335 and 2 assigned to placebo) to evaluate AL-335 dosed once daily for 7 days.
- Compensated cirrhosis: a cohort of ten (10) subjects with CHC genotype 1 infection and documented compensated cirrhosis (Child-Pugh Class A) will be enrolled (8 assigned to AL-335 and 2 assigned to placebo) to evaluate AL-335 dosed once daily for 7 days. Sequence analysis of HCV NS5b from CHC GT1 cohorts assigned to receive either AL-335 or placebo will be completed prior to enrollment of subjects with compensated cirrhosis and CHC GT1.

In Parts 1–2, the doses to be evaluated may be modified based on emerging PK and safety data. However, there will be no more than a three-fold increase in dose per cohort (see *Cohort Progression Guidelines*, Section 5.1.1) and the mean exposure for ALS-022227 (AUC0-24) at a dose level will be projected not to exceed 75,500 ng·h/mL.

In Part 3, the doses to be evaluated may be modified based on emerging PK, HCV RNA and

safety data. However, the maximum dose administered will not exceed the maximum tolerated dose observed in Part 1; the mean exposure for ALS-022227 ( $AUC_{0-24}$ ) at a dose level will be projected not to exceed 75,500 ng·h/mL; and there will be no more than a three-fold increase in dose per cohort (see *Cohort Progression Guidelines*, Section 5.1.1).

In Parts 1–3, an increase in dose will only occur if the previous dose is demonstrated to be generally safe and tolerable (see *Cohort Progression Guidelines*, Section 5.1.1). Before the second and subsequent cohorts are conducted, safety data from the prior cohort will be reviewed by the Principal Investigator (PI) and Sponsor.

Part 3 will commence when the third dose of Part 1 is found to be safe and tolerable based upon a review of the blinded safety data by the PI and the Sponsor. Dosing will take place after a standard meal.

Safety and tolerability will be evaluated on an ongoing basis through assessment of adverse events, blood and urine sample analyses, collection of electrocardiograms (ECG), vital signs and physical examinations. In the event a safety signal is detected, the pharmacokinetic/pharmacodynamic (PK/PD) relationship between AL-335 and its metabolites and various safety parameters including ECG changes, vital signs, and relevant laboratory parameters will be evaluated.

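### Section 7.4 plans the exposure-safety analysis unconditionally, but Sections 2.1 and 10.4.2 run it only after an undefined safety signal; the sections must be reconciled, preferably by dropping the condition.

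*Protocol*

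**What the plan says.** Three places in the protocol describe one analysis, the relation of AL-335 and metabolite exposure to ECG changes, vital signs and relevant laboratory parameters.

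- Section 7.4, without condition: "The PK/PD relationship between AL-335 and its metabolites and various safety parameters including ECG changes, vital signs, and relevant laboratory parameters will be evaluated".
- Section 2.1, with a condition: "In the event a safety signal is detected, the pharmacokinetic/pharmacodynamic (PK/PD) relationship between AL-335 and its metabolites and various safety parameters" will be evaluated.
- Section 10.4.2, with the same condition: "In the event a safety signal is detected, the PK/PD relationship between AL-335 and its metabolites and various safety parameters" will be evaluated.

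No section says what counts as a safety signal.

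In Section 10.4.2, vital signs and physical findings are summarised by cohort and by treatment assignment. Laboratory values are graded and summarised, and the one table specified is this: "Number and percentage of subjects with Grades 3 and 4 laboratory abnormalities will be tabulated by dosing cohort" and by treatment. ECG appears in that section only in its heading and in the conditional sentence. Section 9.2.1 lists 12-lead ECGs among the safety measures to be analysed, without saying how.

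Section 10.0 fixes the cohort sizes. Part 1: "For each dose cohort, 8 subjects will be randomized in a 3:1 ratio to receive AL-335 or placebo", that is 6 and 2. Part 3: "For each dose cohort, 10 subjects will be randomized in a 4:1 ratio to receive AL-335 or placebo", that is 8 and 2.

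**The concern.** The same evaluation is both always done and done only on a trigger. This is not a detail left to the SAP, because the protocol settles it twice in opposite directions and an SAP author must depart from one section. Section 10.4.2 is the one an analyst is likely to follow.

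With the condition in force, someone must decide from the data, without a stated rule, whether to run the analysis that uses the whole dose range. The by-cohort summaries that would inform that decision are weak at showing a graded shift in QTcF, heart rate or a laboratory value. Safety is the primary objective, and Section 3.2.1 names vital signs, 12-lead ECG and laboratory results in the primary endpoint. The report could therefore state that no signal was seen without the analysis best placed to find a graded one.

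**Working it through.** **Text.** Sections 2.1, 7.4 and 10.4.2 name the same drug, metabolites and three groups of safety parameters. They differ only in the opening condition. The protocol gives no power figure for safety, so there is none to reproduce.

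**Could the escalation rules in Section 5.1.1 serve as the signal?** They are not described as its definition. One requires at least 3 subjects in a cohort with sustained QTcF above 500 msec and a rise above 60 msec. Counting the 6 active subjects, binomial P(at least 3) is 1.6% at a true per-subject risk of 10% and 9.9% at 20%. A mean rise of 10 to 20 ms with SD 8 to 15 ms (assumed) would meet the 60 msec part less than 0.001% of the time.

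**Sensitivity of a slope compared with cohort contrasts.** Inputs from the protocol:
- Part 1: 6 active subjects at each of 100, 200, 400, 800 and 1200 mg, and 10 placebo.
- Part 3, planned genotype 1 cohorts: 8 active at each of 400, 600 and 800 mg, and 6 placebo.

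Assumptions, not in the protocol: a true QTcF rise of 10 ms at the top dose of the Part, linear in dose; SD of change 8, 10 or 12 ms; one-sided 5%; noncentral t. Nominal dose stands in for exposure.

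*Two groups:* δ = 10 / [SD × √(1/n₁ + 1/n₂)].

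*Slope:* x = dose / top dose, δ = 10 × √Sxx / SD.
- Part 1: mean x = 6 × 2.25 / 40 = 0.3375; Σx² = 9.542; Sxx = 9.542 − 40 × 0.3375² = 4.985.
- Part 3: mean x = 8 × 2.25 / 30 = 0.60; Σx² = 14.5; Sxx = 14.5 − 30 × 0.36 = 3.70.

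*Worked case, Part 1, SD 10:*
- 6 v 2: δ = 10 / (10 × 0.8165) = 1.22, 6 df, critical value 1.943.
- 6 v 10: δ = 10 / (10 × 0.5164) = 1.94, 14 df, critical value 1.761.
- Slope: δ = 2.233 = 2.23 rounded, 38 df, critical value 1.686.

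| Comparison | SD 8 | SD 10 | SD 12 |
|---|---|---|---|
| Part 1, 1200 mg v own placebo (6 v 2) | 38.7% | 28.9% | 23.1% |
| Part 1, 1200 mg v pooled placebo (6 v 10) | 74.4% | 57.8% | 45.6% |
| Part 1, all active v all placebo (30 v 10) | 44.8% | 33.2% | 26.2% |
| Part 1, slope, 40 subjects | 86.3% | 70.8% | 57.2% |
| Part 3, 800 mg v pooled placebo (8 v 6) | 70.4% | 54.0% | 42.5% |
| Part 3, slope, 30 subjects | 75.8% | 59.2% | 46.8% |

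The 30 v 10 row uses the mean active effect, 10 × 2.25 / 5 = 4.5 ms, because the low doses dilute it.

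Gain of the slope over pooled placebo: 11.9, 13.0 and 11.6 points in Part 1; 5.4, 5.2 and 4.3 points in Part 3.

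**If individual exposure drives the effect.** At a 1 SD effect at the top Part 1 dose, two-sided 5%, simulation with exposure CV 30% and 60% gives 64% and 73% for an exposure slope. The 6 v 10 contrast has 42% and 40%.

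**If only the top dose has an effect.** With 10 ms at 1200 mg and none below, the expected fitted slope is 10 × 6 × (1 − 0.3375) / 4.985 = 7.97. Ignoring the extra residual spread from lack of fit, δ = 7.97 × 2.233 / SD = 2.23, 1.78 and 1.48, below the pooled-placebo values of 2.42, 1.94 and 1.61. The advantage reverses slightly.

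**The case against.** Section 7.4 describes the sponsor's ongoing review of events, so its sentence may belong to monitoring and not to the planned analysis. That reading is possible, but the wording carries no limit, and the sections still disagree.

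Three stronger readings are tempting, and the documents do not support them.

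- **That the small cohort tables are the only possible source of a signal.** Section 9.1 also presents analyses for the combined population. Section 10.4 tabulates by treatment assignment, Section 5.1.1 describes cohort safety reviews with numeric thresholds, and Section 6.2.6 has the investigator evaluate the ECGs. So the 6 v 2 contrast, with a gap of 34 to 47 points to the slope, is not the fair yardstick. Much of that gap comes from pooling placebo.
- **That any effect reported after a signal will be overstated.** This follows only if the trigger is an extreme value of the same outcome. A signal from an adverse event or another parameter need not select the regression outcome in that way.
- **That the missing definition of a signal is itself an error.** The SAP may supply it. The definition matters here because the protocol's own sections conflict on whether a trigger is needed at all.

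It is also fair that the safety summaries are descriptive, so the power of a cohort table is an illustrative device. Nor does the condition forbid the analysis. Pooling all cohorts without care would mix fasted tablet with fed suspension dosing in Part 1, and different genotypes and cirrhosis in Part 3. That last point stands and limits the fix.

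**Conclusion.** The contradiction is in the text and needs no assumption. The loss of sensitivity is real but moderate. Under a linear effect, the planned slope adds about 12 to 13 points of power over the top cohort against pooled placebo in Part 1, and about 4 to 5 points in Part 3. These figures rest on the assumed 10 ms effect, the assumed SDs, linearity, and dose as a proxy for exposure. For an effect confined to the top dose the advantage may shrink or reverse.

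The study is exploratory, no sample-size calculation was made, and no confirmatory test is affected. The point still deserves correction, because it concerns variables named in the primary endpoint and because Section 10.4.2 contains no other ECG analysis.

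**What to change.** Delete the conditional clause in Sections 2.1 and 10.4.2 so that both match Section 7.4. State in Section 10.4.2 that the exposure-safety analysis is a pre-planned exploratory analysis, done within each Part:

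- Relate change from baseline in QTcF, heart rate and key laboratory values to subject exposure (Cmax or AUC), with placebo at zero exposure.
- Limit the main model to comparable cohorts: the fasted tablet cohorts 1 to 5 in Part 1, and the non-cirrhotic genotype 1 cohorts in Part 3. Otherwise include terms for food and formulation, or for population.
- Label the intervals exploratory and unadjusted for multiplicity.

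If the sponsor prefers to keep the condition, the minimum is to define the signal in advance and align Section 7.4 with it. That restores consistency but leaves the graded effect to the cohort summaries.

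The cost is one clause removed in two places and one further set of models on data already scheduled for collection. The downside is more output to interpret: with several analytes, exposure measures and outcomes, some chance positives must be expected.
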